#### Mechanistic studies outcome measures

The identification of novel markers could augment current practice by predicting the outcome of each liver with objectivity. The mechanistic studies will test hypotheses based on previous published studies that have investigated markers in the field of NMP and will inform development of functional criteria and optimisation of future defatting protocols:To measure the effect of the intervention on the histological degree of steatosis:Histological quantification of MaS measured pre-perfusion, post-perfusion and during re-perfusion in the recipient. We hypothesise that the intervention of defatting will reduce the degree of MaS and severity of NAFLD activity score [75].To measure the effect of the intervention on markers on of hepatic lipid metabolism:Perfusate TG, insulin, ketone bodies and cytokines associated with IRI will be measured at baseline (pre-NMP) and during preservation (1, 2, 4 and 6 h and end of perfusion). Further measurements taken from the recipient peri-operatively (before transplant) and re-perfusion (following liver transplantation). This will provide insight into changes in intrahepatic lipid handling and inflammation. We hypothesise that the intervention of defatting will ‘repartition’ intrahepatic fatty acids away from esterification into oxidation pathways leading to a decrease in IHTG and a decrease in IRI-associated cytokine production [70].Perfusate FGF-21 will be measured at baseline (pre-NMP) and during preservation (1, 2, 4 and 6 h and end of perfusion). Further measurements taken from the recipient peri-operatively (before transplant) and re-perfusion (following liver transplantation). FGF-21 is a hormone produced in the liver involved in energy homeostasis; its secretion is attributed to metabolic stress. There is evidence that serum FGF-21 is a useful marker for steatosis and correlates with increasing steatosis grade [76]. We hypothesise that the defatting intervention will reduce FGF-21.To understand the structural, cellular and metabolic effects of defatting on steatotic livers.Genomic analysis of samples taken pre-perfusion, post-perfusion and following re-perfusion in the recipient:◦Transcriptomics: a complex signalling cascade regulates metabolic processes within the liver. To understand the effect of NMP and the defatting intervention, genomic analysis of liver tissue will be undertaken. We hypothesise that the defatting intervention will lead to downregulation in pathways related to fat synthesis and inflammation and an upregulation in pathways related to fat disposal. Samples from livers will undergo RNA sequencing of the liver and this will be correlated with clinical outcomes. Changes in gene expression will be mapped with changes occurring in biological pathways, inferring biological changes during NMP.Proteomic and glycomic analysis of perfusate samples taken at baseline (pre-NMP) and during preservation. Further measurements taken from the recipient peri-operatively (before transplant) and re-perfusion (following liver transplantation):◦Proteomics: a recent study investigating the use of NMP to increase utilisation of high-risk donor livers, identified protein clusters that were able to discriminate between transplantable and non-transplantable livers (22 out of 31) as well as markers predictive of post-transplant complications [77]. We aim to determine the effect of the intervention on protein expression associated with hepatic steatosis, inflammation and IRI.◦Glycomics: the liver perfusate glycome profile may form part of future functional criteria [78]. A recent study found that the abundance of a single glycan, agalacto core-alpha-1,6-fucosylated biantennary glycan (NGA2F) was significantly higher in the perfusate of livers that developed PNF. We will test this hypothesis in sequential perfusate samples.

### Participant timeline {13}

The proposed study duration is 56 months (01/04/2021 – 30/11/2025): The DeFat study set-up tasks commenced in April 2021 and the study opened for recruitment on the 23rd of February 2023. The anticipated end date for recruitment is the 30th of November 2024 (total recruitment period of 21 months) with 6 month follow-up of the last participant and 6 months analysis/dissemination (close-out) anticipated to be completed by the 30th November 2025. The flow of participants in the study is summarised in Fig. 6. In addition, all trial procedures are summarised in Table 3 (Standard Protocol Items: Recommendations For Interventional Trials, SPIRIT).

**Fig. 6 Fig6:**
[figure not shown]
Flow of participants through the study. NMP normothermic machine perfusion, MRCP magnetic resonance cholangiopancreatography, ALT alanine transaminase

**Table 3 Tab3:** SPIRIT table of enrolment, interventions, and assessments (schedule of procedures)

**Activity**	**Pre-study screening**	**Pre-study baseline**	**Pre-perfusion**	**During and end of perfusion**	**Pre-transplant**	**Post-reperfusion**	**Postoperative**									**Follow-up and close-out**			
							D1	D2	D3	D4	D5	D6	D7	D10	D14	D30	M3	M6	Close-out
**Informed consent**	X																		
**Meets inclusion/exclusion criteria**	X																		
**Randomisation**		X																	
**Donor and recipient demographics**		X																	
**Perfusion parameters and samples**			X	X	X	X													
**cfDNA samples**			X	X	X	X	X		X				X		X	X	X	X	
**Surgical variables**						X													
**Serum ALT and AST**							X	X	X	X	X	X	X			X	X	X	X
**Serum bilirubin**							X	X	X	X	X	X	X			X	X	X	X
**Serum GGT**							X	X	X	X	X	X	X			X	X	X	X
**INR**							X	X	X	X	X	X	X			X	X	X	X
**Serum lactate***							X	X	X	X	X	X	X						
**Primary non-function**														X					
**Graft survival**							X	X	X	X	X	X	X	X		X	X	X	X
**Patient survival**							X	X	X	X	X	X	X	X		X	X	X	X
**Resource use**							X	X	X	X	X	X	X	X		X	X	X	X
**Safety outcomes**						X	X	X	X	X	X	X	X	X		X	X	X	X
**MRI (depending on site capacity)**																		X	

#### Baseline donor and recipient assessment

Baseline donor assessments will include donor demographics and blood test results. The following information will be recorded: age, sex, ethnicity, co-morbidities, cause of death, height, weight, BMI, WC, smoking history and alcohol consumption. Donor blood test will include last and peak serum aspartate transaminase (AST), alanine transaminase (ALT), gamma-glutamyl transferase (GGT) and serum bilirubin and sodium. Other donor information will include last and fasting triglyceride (TG), if available, evidence of TPN or enteral feed (if information available) and length of ITU stay.

Baseline recipient demographics will include recipient demographic and pre-transplant test results. The following information will be recorded: age, sex, ethnicity, co-morbidities, at the time of transplant (minimum 24 h of continuous renal replacement therapy) or two haemodialysis sessions in the previous week, aetiology of primary liver disease and primary indication of transplant, height, weight, BMI, WC (where available) and smoking history. Pre-transplant recipient blood test will include INR, creatinine, bilirubin and sodium.

#### Donor timings

These are all routinely collected at the time of retrieval and will be obtained from the NHSBT database.

The parameters to be recorded include:Timings:◦ Withdrawal of support (DCD donors only)◦ Onset of functional warm ischaemia (DCD donors only)◦ Cessation of donor circulation (cross clamp or asystole in DCD donors)◦ Start of cold perfusion◦ Liver removal and placement on icePerfusion solution used for aortic perfusionPerfusion solution used for storage and transportDegree of steatosis (graded mild, moderate, severe)—surgeon’s assessmentQuality of in situ perfusion (graded poor, moderate, good)

#### Preservation parameters

In addition to timings, a number of other preservation parameters will be recorded. These will include:Time of initiation of normothermic machine preservationTime of cessation of normothermic machine preservation (end flush)Flush solution (UW, HTK, other)Perfusion parameters (for NMP livers; logged automatically by the device):◦Arterial and caval pressures (in mmHg)◦ Arterial, portal and caval flow rates (in L/min)◦ pO_2_, pCO_2_ and pH◦ Blood temperature (°C), glucose (mmol/L) and bile production (mL/h)Perfusate biochemistry◦ Perfusate lactate at baseline (pre-NMP), 5 min after start of NMP and during preservation (1, 2, 4 and 6 h and the end of NMP)◦ Perfusate pH at baseline (pre-NMP) and during preservation (1, 2, 4 and 6 h and end of NMP)◦ Perfusate ALT at baseline (pre-NMP) and during preservation (1, 2, 4 and 6 h and end of NMP)◦ Glucose levels at baseline (pre-NMP) and during preservation (1, 2, 4 and 6 h and at the end of NMP)◦ Bile pH, glucose and bicarbonate (if bile produced) at 1, 2, 4 and 6 h and at the end of NMP◦ Bicarbonate use (time and dose of each bolus)Sampling:◦ Perfusate at baseline (pre-NMP) and during preservation (1, 2, 4 and 6 h and end of NMP)◦ Liver core biopsies taken pre-perfusion and post-perfusion◦ Bile duct biopsies taken pre-perfusion and post-perfusion where feasible, i.e. if sufficient bile duct length

At the end of preservation, a sample of perfusate/storage solution will be taken for microbiological culture as per standard practice.

Operative parameters

These will include:Total operative time: defined as time from knife-to-skin to skin closureTime of flush at end of NMPTime of liver in body (start of anastomosis)Time of reperfusion (portal or arterial, whichever occurs first)Portal reperfusion timeArterial reperfusion timeIntraoperative transfusion of blood products measured in unitsThe use of veno-venous bypass or porto-caval shuntsType of caval anastomosis (standard end-end, piggyback (end-side or side-side))

#### Intra-operative outcome assessment

Recipient blood samples (before and after transplant) and post-reperfusion liver biopsy (as well as bile duct biopsy where feasible) will be taken:◦ Peri-operative blood taken (before transplant) and re-perfusion (following liver transplantation)◦ Liver core biopsy taken post-reperfusion◦ Bile duct biopsy taken post-reperfusion where feasible i.e. if sufficient bile duct length

These samples will be taken to determine the severity of ischaemia–reperfusion injury and changes in mean arterial pressure will be recorded to assess for post-reperfusion syndrome:Histological and biochemical evidence of ischaemia–reperfusion injury (IRI) in recipient [70]:Cytokine profile implicated in liver transplantation including [70]: CXCl8/IL-8, IL-10, IL-2, TNF-a, IFN-γ, IL-13, IL-4, IL-1β, IL-17A and IL-6.Liver histology (formalin fixed paraffin embedded biopsy) [33]:Neutrophil infiltration and leucocytosis determined using haematoxylin and eosin (H&E) stainGlycogen depletion determined using periodic acid-Schiff (PAS) stainLipid peroxidation determined using 4-HNE (4-hydroxynonenal) stainBile duct histology (formalin fixed paraffin embedded biopsy) [71]:Evidence of stroma necrosis, extramural peribiliary glands (loss/injury to cells) and presence of vascular lesionsPost-reperfusion syndrome (PRS) [65], a decrease in mean arterial pressure (MAP) of more than 30% for more than 1 min during the first 5 min after reperfusion [65].

#### Declines and discards

If a decision is made to decline an organ at any point after retrieval (but before randomisation), any donor and preservation data recorded will be kept, and the reason for decline clearly documented in the eCRF. If deemed appropriate by the OTDT Hub, the organ may be offered to other centres on the matching run with liver allocation as per standard of care. If the liver is already on the OrganOx *metra*^*®*^ device, every attempt should be made to keep it on the device (as per national agreement). If all centres subsequently decline an organ, the organ will be documented as a discard and it will be offered for research or disposed of as per standard procedures.

Data will also be collected for all discards (including reason for discard) from point of randomisation.

#### Inpatient stay

Patients will be assessed daily by their clinical team and managed according to standard care protocols at the site with clinical information obtained from medical records.

Post-operative outcome assessment

The investigations performed form part of routine clinical care.

The following biochemical outcomes will be recorded:Daily serum samples for the first 7 days post-transplant, to include:◦ Serum bilirubin (measured in μmol/l)◦ Serum gamma-glutamyl transferase (GGT; measured in IU/L)◦ Serum aspartate transaminase (AST; measured in IU/L) or serum alanine transaminase (ALT; measured in IU/L) depending on liver transplant centre◦ International normalised ratio (INR)◦ Serum alkaline phosphatase (ALP; measured in IU/L)◦ Blood urea (mmol/L)◦ Serum creatinine (μmol/L)Daily serum lactate (measured in mmol/L) whilst on ITU/HDU.

The first measurements should be taken at 12 to 24 (±6 h) hours post-transplant. For subsequent measurements, in the event that more than one measurement is taken in a 24-h period, the measurement taken closest to the specified follow-up time-point should be used.cfDNA measurements perioperatively in the recipient (before and after transplant) and on days 1, 3, 7 and 14 (if the patient is discharged prior to day 14—a sample will be collected on the day of discharge instead). cfDNA has been correlated with allograft injury, rejection and formation of de novo donor specific antibodies [61]. These research samples will be taken alongside routine clinical samples in order to minimise any additional tests.Model of Early Allograft Function (MEAF) [64]: a score (between 0 and 10) based on bilirubin, INR and ALT within the first three post-operative days.

Other outcomes to be recorded include:Length of stay in level 2/level 3 care (ITU/HDU) (days)Total length of hospital stay (days)Requirement for renal replacement therapy during transplant admission (haemodialysis (HD), haemodiafiltration (HDF), haemofiltration (HF), peritoneal dialysis (PFD))Graft and patient survival at day 7 post-transplantPrimary non-function: irreversible graft dysfunction requiring emergency liver replacement during the first 10 days after liver transplantation, in the absence of technical or immunological causes.

Safety outcomesRecipient infection (defined as both clinically diagnosed treated infection and infection with a positive microbiological culture result)Clinically suspected treated rejectionBiopsy-proven acute rejection episodesBiliary complications diagnosed radiologically, e.g. a non-protocol MRI or CT scan in clinically symptomatic patient:◦Biliary strictures——anastomotic and non-anastomotic. Defined as those requiring surgical or radiological intervention◦Bile duct leaks. Defined as those requiring drainage, refashioning of anastomosis or stenting.Vascular complications◦Bleeding. Defined as bleeding requiring transfusion and/or radiological/surgical intervention.◦Hepatic artery stenosis. Defined as causing graft dysfunction requiring radiological or surgical intervention or resulting in graft loss.◦Hepatic artery thrombosis. Defined as formation of new clot resulting in graft dysfunction or loss, or requiring pharmacological, radiological or surgical intervention.◦Portal vein thrombosis. Defined as formation of new clot resulting in graft dysfunction or loss, or requiring pharmacological, radiological or surgical intervention.◦Portal vein stenosis. Defined as causing graft dysfunction requiring radiological or surgical intervention or resulting in graft loss.◦IVC/hepatic vein occlusion. Defined as formation of new clot resulting in graft dysfunction or loss, or requiring pharmacological, radiological or surgical intervention.Reoperation rateTechnical complications and device failuresAny other reported adverse event

Severity will be graded according to the Clavien–Dindo classification [66]—*Supplemental *Table 1.

Immunosuppression

Details of induction immunosuppression and maintenance immunosuppression (including doses) at day 7 post-transplant will be recorded.

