#### Secondary outcome measures

ClinicalProportion of livers transplanted in the two armsLiMAx (maximum liver function capacity) test performed after 1 h of liver stabilisation during NMP, repeated at 5 h and subsequently every 6 h till end of perfusion where feasible. If the decision to transplant has been made by 6 h of NMP, the test will not be repeated. The LiMAx test will allow real-time monitoring of CYP1A2 (prominent in functional livers cells and less prominent in damaged cells) and is based on the metabolism of ^13^C-methacetin. This will enable measurement of liver capacity and functional reserve during perfusion [60].Cell-free DNA (cfDNA) measured at baseline (pre-NMP) and during preservation (1, 2, 4 and 6 h and end of perfusion). Further measurements taken from the recipient peri-operatively (before transplant) and re-perfusion (following liver transplantation). Post-operative samples collected on days 1, 3, 7 and 14 (if the patient is discharged prior to day 14—a sample will be collected on the day of discharge instead). Outpatient sample collection will align with clinic visits on day 30 and months 3 and 6. cfDNA has been correlated with allograft injury, rejection and formation of de novo donor-specific antibodies [61].Biochemical liver function in the first 7 days post-transplant: ALT, GGT, INR, bilirubin and peak serum AST (where AST measurements available) in the first 7 days post-transplant. Peak serum AST is a validated surrogate marker, predictive of PNF as well as graft and patient survival [62]. It is also associated with histological evidence of moderate to severe reperfusion injury [63].Model of Early Allograft Function (MEAF) [64]: a score (between 0 and 10) based on bilirubin, INR and ALT within the first three post-operative days.Primary non-function (PNF): irreversible graft dysfunction requiring emergency liver replacement during the first 10 days after liver transplantation, in the absence of technical or immunological causes.Post-reperfusion syndrome (PRS) [65]: a decrease in mean arterial pressure (MAP) of more than 30% for more than 1 min during the first 5 min after reperfusion [65].Need for renal replacement therapy (haemodialysis, haemofiltration, peritoneal dialysis) during the first 7 days post-operatively.Duration of ITU/HDU and hospital stay.Graft survival (defined as a functioning transplant in the absence of death and re-transplantation) at day 7, day 30, month 3 and month 6.Patient survival at day 7, day 30 and months 3 and month 6. In addition, 12-month clinical outcomes (obtained from NHSBT registry) will also be reported:aGraft and patient survivalbTotal number of days in hospital in the last year (excluding transplant admission)cTotal number of re-admissions for:•Recipient infection•Acute rejection•Chronic rejection•Biliary complications•Vascular complications•Disease recurrence•Other reasonsdTransplant-related renal dysfunctioneBiochemistry (liver and renal function)The following safety information will be recorded:aOrgan discard ratebPerfusate culture. At the end of preservation, a sample will be taken for microbiological culture.cAdverse event rates and severity, graded according to the Clavien–Dindo classification [66] during the first 7 days, day 30, month 3 and month 6:•Recipient infection•Biopsy proven acute rejection•Biliary complications (biliary strictures—anastomotic and non-anastomotic, bile duct leaks)•Vascular complications (bleeding, hepatic artery stenosis, hepatic artery thrombosis, portal vein thrombosis)•Reoperation ratedTechnical complications/device failures

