ImagingBiliary strictures (anastomotic and non-anastomotic) determined by MRI scan at month 6 (±1 month) depending on site capacity using MRCP^+^ (a CE-marked advanced biliary visualisation software by Perspectum Diagnostics) [72].Graft hepatic steatosis determined using multiparametric liver MRI (proton density fat fraction, cT1 and T2* mapping) at 6 (± 1 month) depending on site capacity. MRI proton density fat fraction (MRI-PDFF) has demonstrated high diagnostic accuracy in both the detection and grading of hepatic steatosis with histology as a reference standard [73, 74]. CE-marked software such as Liver*MultiScan*^TM^ developed by Perspectum Diagnostics will aide in the quantification of steatosis.

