Safety	• Recipient infection^a^ • Clinically suspected treated rejection • Biopsy-proven acute rejection • Biliary complications^b (i-ii)^ • Vascular complications^c (i-vi)^ • Reoperation rate • Technical complications and device failures • Any other reported adverse event	• Recipient infection^a^ • Biopsy-proven acute rejection • Biliary complications^b (i-ii)^ • Vascular complications^c (i-vi)^ • Reoperation rate • Technical complications and device failures • Any other reported adverse event	• Recipient infection (CMV infection, fungal infection, post-operative sepsis) • Biopsy-proven acute rejection episodes • Biliary complications^b (i-ii)^ • Vascular complications^c (i-vi)^ • Reoperation rate • Technical complications and device failures • Any other reported adverse event	• Recipient infection (CMV infection, fungal infection, post-operative sepsis) • Biopsy-proven acute rejection episodes • Biliary complications^b (i)^ • Vascular complications^c (i-vi)^ • Reoperation rate • Technical complications and device failures • Any other reported adverse event
Immunosuppression	Immunosuppression regimen at day 7 (including doses)	Immunosuppression regimen at day 30 (including doses)	Immunosuppression regimen at month 3 (including doses)	Immunosuppression regimen at month 6 (including doses)

^a^Infection, defined as both clinically diagnosed treated infection and infection with a positive microbiological culture result

^b^Biliary complications diagnosed radiologically, e.g. a non-protocol MRI or CT scan in clinically symptomatic patient: (i) biliary strictures—anastomotic and non-anastomotic. Defined as those requiring surgical or radiological intervention and (ii) bile duct leaks. Defined as those requiring drainage, refashioning of anastomosis or stenting

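### The biliary stricture safety definition names only surgical and radiological treatment, so strictures treated only by endoscopy may be left out of the biliary complication rate or counted differently between sites

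*Protocol article*

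**What the plan says.** The secondary outcome measures include, among the safety items graded by Clavien–Dindo over the first 7 days and at day 30, month 3 and month 6, "Biliary complications (biliary strictures—anastomotic and non-anastomotic, bile duct leaks". No treatment condition is attached there.

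The safety outcomes list under the inpatient stay adds two conditions. The first concerns how the event is found: "Biliary complications diagnosed radiologically, e.g. a non-protocol MRI or CT scan in clinically symptomatic patient". The second concerns strictures specifically: "Defined as those requiring surgical or radiological intervention". Bile duct leaks, the next item, have a different rule: "Defined as those requiring drainage, refashioning of anastomosis or stenting".

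Table 4, footnote b, repeats the stricture rule for the study visits: "biliary strictures—anastomotic and non-anastomotic. Defined as those requiring surgical or radiological intervention".

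Separately, the imaging endpoints include strictures of both types "determined by MRI scan at month 6 (±1 month) depending on site capacity", with no reference to treatment.

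**The concern.** The stricture rule lists two routes of treatment and omits endoscopy. A site that applies it as written would record an endoscopically stented leak as a biliary complication, but not a stricture stented in the same way. A site that regards fluoroscopy-guided endoscopy as radiological would record both.

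Confirming safety is part of the primary objective, and the statistical methods section wants effect sizes with confidence intervals to help design a definitive trial. Recipient outcomes come only from transplanted livers, so at most 30 per arm contribute. With numbers this small, one or two reclassified events visibly change the estimate. Five centres recruit, and randomisation is stratified by donor type, not by centre, so different site readings would add noise that the design does not balance.

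**Working it through.** The plan states no figure for this point. The check is a comparison of text, followed by an illustration on assumed values.

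**Comparison of the definitions**

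| Place | Event | Condition for counting |
|---|---|---|
| Secondary outcome measures, safety | Stricture | None stated |
| Safety outcomes list (inpatient stay) | Stricture | Surgical or radiological treatment needed |
| Table 4, footnote b | Stricture | The same |
| Safety outcomes list and footnote b | Bile leak | Drainage, refashioning or stenting; no route named |
| Safety outcomes list and footnote c | Hepatic artery or portal vein thrombosis | Graft dysfunction or loss, or treatment by drug, radiology or surgery |
| Imaging endpoints | Stricture | Seen on the month-6 MRI; treatment irrelevant |

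Four things follow.

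1. The stricture wording appears twice in the same form, so it is not an isolated slip.
2. The lists of routes vary from one event to the next. A reader has reason to treat each list as complete.
3. The safety outcomes list is narrower than the secondary outcome list that it is meant to specify.
4. At month 6, Table 4 limits biliary complications to part (i) of footnote b, which is strictures alone. The biliary safety item at that visit therefore rests entirely on this definition.

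**Illustration of size**

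Let r be the true rate of treated strictures and f the share treated only endoscopically. If every site reads the rule literally, the recorded rate is r × (1 − f), and the expected number missed among 30 recipients is 30 × r × f. Thirty is the ceiling per arm, reached only if every randomised liver is transplanted. Both r and f are assumptions; the article gives neither.

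| True rate r | f = 0 | f = 25% | f = 50% | f = 75% |
|---|---|---|---|---|
| 10% | 10% (0 missed) | 7.5% (0.75) | 5% (1.5) | 2.5% (2.25) |
| 20% | 20% (0) | 15% (1.5) | 10% (3.0) | 5% (4.5) |
| 30% | 30% (0) | 22.5% (2.25) | 15% (4.5) | 7.5% (6.75) |

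For example, with r = 20% and f = 50%: 0.20 × (1 − 0.50) = 0.10, and 30 × 0.20 × 0.50 = 3.0. If all sites class endoscopic treatment under fluoroscopy as radiological, and all such treatment is done that way, the f = 0 column applies whatever the treatment mix.

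**The case against.** The strongest reply is that the article never mentions endoscopy, gives no treatment mix and does not say how fluoroscopy-guided endoscopy is classed. Nothing in it shows that any event will be lost. This stands, and it limits the claim to what may happen. A reader might infer that endoscopically treated strictures are certainly uncounted and the rate certainly too low; the documents do not support that. The table above only restates its assumptions.

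A second reply is that such strictures are recorded elsewhere. Serious adverse events are collected until 6 months after transplant, and in-patient care or prolonged hospitalisation makes an event serious. Table 4 has a row entry for "Any other reported adverse event". The 12-month registry data count re-admissions for biliary complications. The month-6 MRI may show a stricture. So a reader should not infer that a treated stricture goes unrecorded. However, none of these routes puts it in the defined biliary complication rate, and they are incomplete: the MRI depends on site capacity, and non-serious events are documented only if the investigator thinks them likely to be associated with the intervention.

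A third reply concerns reach. The abstract names non-anastomotic strictures as an endpoint, and a reader might infer that this headline endpoint is compromised. The abstract's wording appears to refer to the separate MRI endpoint, which has no treatment condition. Local teams are also blinded, so classification should not depend on arm, and little testing of secondary endpoints is planned. These points stand.

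Finally, this is a condensed article, and a study manual and the eCRF, neither shown, may settle the coding. That would excuse missing detail. Here the article states a rule, states it twice, and the rule as stated is too narrow.

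**Conclusion.** The point holds as a fault in a stated outcome definition. Read literally, the stricture rule leaves out strictures treated only endoscopically, and it agrees neither with the leak definition beside it nor with the unconditional listing in the secondary outcome measures. The biliary complication rate may be understated in both arms, or recorded differently between sites.

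The size is unknown. It ranges from nil, if no stricture is treated only endoscopically or all sites read the rule inclusively, to a material share of the events if that share is large and sites read the rule literally. The wording is the same for both arms and gives no ground for claiming that it favours either one. The month-6 MRI stricture endpoint, the primary endpoint of function at 6 hours of perfusion, its analysis and the sample size are not touched.

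**What to change.** In the safety outcomes list and in Table 4, footnote b, define the event as a stricture requiring surgical, radiological or endoscopic intervention, meaning dilatation or stenting by any route. Make the secondary outcome list refer to that definition. Add a field for the route of treatment to the eCRF, and recheck strictures already entered against hospital records.

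Keep strictures found only on the protocol MRI in the separate imaging endpoint. The safety item rests on non-protocol diagnosis in patients with symptoms, and mixing the two would make the safety rate depend on which sites have MRI capacity.

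The cost is one phrase in two places, a cross-reference, one eCRF field and a limited record check. The reported complication rate may be somewhat higher. Patient care does not change.
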